### Study population

Participant eligibility criteria include the following: (1) Female; (2) Black African; (3) Aged 15 or older (if under 18, must be able to demonstrate the criteria for tacit emancipation according to South African law); (4) Report using at least one of the following drugs weekly during the past 90 days—alcohol, marijuana (dagga), methamphetamine (tik), methaqualone (Mandrax), cocaine (crack and/or powder), heroin (Thai White), inhalants (glue and benzene), MDMA (ecstasy), LSD, methcathinone (Kat/cat), or marijuana and heroin mixed (Nyaope); (5) Report having unprotected vaginal sex with a male partner in the past 6 months; (6) Speaks English, Sesotho, Tswana, or Zulu; (7) Consent to HIV rapid testing and drug testing; (8) Provide written and verbal assent/consent to participate; and (9) Provide verifiable locator information (e.g., house, street corner, vacant lot) for the Pretoria area and plan to stay in the area for the next 12 months. Exclusion criteria include the following: (1) Male; and (2) Self-identify as other than Black African.

### Ethical approval

This study is approved by the South African Medical Association Research Ethics Committee (SAMAREC), Tshwane Research Committee (TRC), and the RTI International Committee for the Protection of Human Subjects. All participants are required to give their informed consent prior to any study procedure. We obtained a waiver for parental consent for participants under the age of consent, which in South Africa is 18 years. Adolescents aged 12 or older can legally consent to HIV testing and medical treatment in South Africa. Also, minors having children, owning a business, or having an occupation that brings in a salary and residence outside the parental home are recognized as emancipated.

When we collect locator information, we explain to the women that we will be coming to look for them for their follow-up visits. Outreach workers are trained to describe the project as a health project, and they are also trained not to disclose any confidential information. All of our staff complete ethics training annually.

### Data and Safety Monitoring Board

The study has established a Data and Safety Monitoring Board (DSMB) comprising expert physicians in infectious diseases, epidemiology, HIV treatment in South Africa, and bioethics. One physician resides in South Africa and treats patients, one is a bioethicist, and the chair is also an infectious disease physician and epidemiologist. The DSMB receives progress reports and meets biannually with the investigators and receives notification and information regarding the circumstances surrounding any participant deaths.

As specified in our Data and Safety Monitoring Plan (DSMP), Severe Adverse Events (SAEs) are reported to the Principal Investigator within 24 hours and to the DSMB, the funding agency and the Institutional Review Board within 48 hours, with appropriate action taken immediately.

### Study procedures

#### Recruitment

Outreach workers actively market the study in each of the zones to recruit participants. The outreach model evolved from a long history of outreach work that started in North Carolina [26], which was later modified for use in Pretoria and Cape Town [27, 28]. We trained the outreach workers on how to market the study in the zones and how to find female sex workers and other vulnerable women who use AOD. The training also includes activities to ensure that outreach workers are aware of safety measures and how to avoid potentially dangerous situations they may encounter. Outreach workers conduct outreach in a wide range of settings that vulnerable women frequent, including daily-rate hotels, taverns, pool halls, brothels, bushes and thickets, and on street corners. Outreach workers also market the study to “big mammas” (madams) and pimps who often serve as gatekeepers for sex workers.

To enroll in the study, eligible participants travel to the field site where the baseline appointment takes place. If participants are not able to come to the field site, interviews may be conducted in a private setting at or near the participant’s residence or place of work. In these instances staff follow a protocol to ensure confidentiality. All outreach workers are familiar with the city of Pretoria and fluent in the local languages, and they are trained on how to approach, screen, and recruit marginalized and stigmatized vulnerable women.

#### Modifications to the protocol

##### Recruitment

Originally, we proposed to recruit the sample by placing mobile units in selected “hotspots” for both study arms to serve as recruitment venues. The hotspots are well-known areas in the community. In the areas randomized to the treatment arm, we planned to enhance recruitment with active outreach to bring women to the mobile unit. However, when funding for the study was awarded, the mobile units were no longer available. This required us to divide the entire city of Pretoria into zones. Consequently, outreach workers market the study and recruit women as described above and they are brought to a field site in the center of the city.

##### Eligibility criteria

The original eligibility criteria included the use of two drugs (one of which could be alcohol) at least weekly. These criteria excluded a large proportion of sex workers and other high-risk women, many of whom were HIV positive. Therefore, we changed eligibility criteria to the use of alcohol or another drug at least weekly.

##### Intake process

In most instances, staff conduct the intake process (i.e., informed consent, baseline interview, biological testing) at the field site. However, in instances in which a participant is not able to come into the field site, project staff conduct the intake in a private setting in the field.

##### Intervention case management

We initially planned to conduct case management weekly using cell phones in most instances. However, many women did not have cell phones, so staff had to conduct case management face to face in many instances, which was more labor intensive. To offset this burden on staff, we reduced the frequency of case management from weekly to monthly.

##### Sample size

We reduced the sample size from 1050 to 600 minimum. The section on sample size includes a description of the rationale for this change.

##### Changes in incentives

We increased the incentives for baseline interviews from R70 to R100 ($1 US equals approximately 10 Rand). We also increased the incentives for 6-month follow-up interviews from R100 to R150 and for 12-month interviews from R150 to R200.

##### Miscellaneous changes

Local HIV clinics required CD4 cell count tests before starting patients on ART. However, there was a backlog for CD4 testing, which resulted in extensive delays in starting ART. To remove this barrier, we began providing onsite CD4 testing. Some women who were on ART reported not having a secure place to store their ARVs. To alleviate this problem, we began storing ARVs for women who did not have a place to store them. We also began conducting some follow-up interviews in private settings in the field if a participant could not come to the field site. We began collecting dried bloodspots for future HIV viral load testing. This was necessary because many HIV clinics were unable to provide HIV viral load test results, and there was no source of viral information for women who were not in HIV treatment (see Table 1 for a list of modifications by date).

**Table 1 Tab1:** **Modifications to the protocol**

Date	Amendment
6/2012	Started completing full intake process (i.e., consent, biological testing, and baseline interview) in the field in addition to the field site.
6/2012	Dropped recruitment through mobile units and added recruitment through outreach workers with most activities conducted at fixed field site. [Note: mobile units were never used to recruit any participants for the study]
6/2012	Reduced frequency of case management from weekly to monthly.
11/2012	Changed eligibility criteria from weekly use of 2 or more drugs (including alcohol) to weekly use of 1 or more drugs (including alcohol).
12/2012	Provided space onsite to store ARVs for participants who did not have a place to store them.
10/2013	Reduced proposed sample from 1050 to 600 minimum.
12/2013	Added onsite CD4 testing.
1/2014	Started completing some follow-up interviews in the field when participants were unable to return to the field site.
5/2014	Increased incentives for baseline interview from R70 to R100; for 6-month follow-up interviews from R100 to R150; and for 12-month follow-up interviews from R150 to R200. [Note: Rand to Dollar conversion rate is approximately R10 = US $1]
5/2014	Began collecting and storing dried bloodspots for future HIV viral load testing.

#### Study activities by arm

##### Control arm

Participants in the control arm receive the “standard HIV counseling and testing” protocol performed in South Africa. At intake, participants complete an interviewer-administered baseline assessment [27] using Computer-Assisted Personal Interviewing (CAPI) technology. Project staff collect biological specimens and test them for evidence of recent drug use, for pregnancy, and for HIV. They also provide HIV pretest and posttest counseling. If a participant tests positive for HIV, her posttest counseling is followed by CD4 testing, which is done onsite immediately afterward using a PIMA™ analyzer (http://pimatest.com/en/home.html). In accordance with medical practice in South Africa, after receiving the CD4 test results, the participant is referred to the appropriate clinic for further medical evaluation and clinical staging that determines whether she is eligible to initiate ART (CD4<350). If the participant initiates ART, she receives adherence counseling through the health department clinic and a full battery of tests (blood count, liver function, and kidney tests) in preparation for ART initiation. The participant also receives CD4 testing at 6- and 12-month follow-up visits. HIV-positive people who are not eligible to receive ART because their CD4 cell count is >350 are referred to a “wellness program.” The local health department clinics operate the wellness programs, which provide access to support groups, ongoing adherence counseling, and information about reproductive health, nutrition, and positive living. When appropriate, the project field staff also provides referrals for pregnancy services, tuberculosis testing, substance abuse rehabilitation, and professional counseling for gender-based violence. Staff members also provide simple meals and coordinate childcare for women in the study during their appointments. They also arrange transportation to the field site for the appointments.

#### Intervention arm

Women in the intervention arm participate in all of the activities described above for the control arm. In addition, they participate in two individual, woman-focused HIV prevention intervention sessions. These sessions aim to increase knowledge, skills, and motivation to make behavioral changes related to AOD use, sexual risk, and violence and victimization. These sessions take place at the field site and are facilitated by an experienced female interventionist who is a multilingual peer leader from the community and who also is sensitive to helping women develop empowerment strategies with a personalized plan after the intervention session.

The WHC is an evidence-based, woman-focused, behavioral intervention that reaches high-risk, hard-to-reach, vulnerable women. It addresses the intersecting risks of drug use, sex behaviors, violence and victimization, with the primary goal of increasing skills and knowledge. The WHC has been adapted from previous iterations in North Carolina, Rhode Island, Massachusetts, Russia, the Republic of Georgia, and South Africa. It is based on social cognitive theory and empowerment theory [29]. Two intervention sessions are held approximately 3 to 5 days apart. Each session lasts 30 to 45 minutes. Key elements of the sessions educate participants about the risks of AOD use and how AOD use and sex risk relate to HIV for women. The sessions also teach risk-reduction methods such as proper condom use, sexual negotiation, and violence prevention strategies. Women also role-play and rehearse how to use male and female condoms correctly, as well as condom negotiation. During the sessions, the women create personalized action plans in which they develop a concrete plan to reduce risk. At the end of the second session, the participant completes the personalized plan, which she takes home as a guideline for her set goals. The staff conducts case management face to face or by cell phone at least monthly to follow up and support the participant in her risk-reduction and action plan to improve her life. For women with AOD use problems, the interventionists work closely with drug rehabilitation facilities to secure treatment slots.

Because this adaptation of the WHC combines TTR activities with a specific focus on linking women to care if they are newly or previously diagnosed with HIV before enrollment, we named this combined biobehavioral intervention the Women’s Health CoOp Plus (WHC+).

#### Outcome measures

The primary outcome is self-reported male or female condom use during the participant’s most recent episode of vaginal or anal intercourse. Other outcomes include frequency of condom use, frequency and quantity of alcohol use, urine drug screen results for illicit substance use, and frequency of violent victimization (physical or sexual). Additional outcomes for women living with HIV include receiving HIV treatment, ART adherence, and CD4 counts. Analyses for HIV-RNA viral load on stored dried blood spots at follow-up may occur at a later date.

Alcohol use is measured biologically with a breathalyzer test and through self-report. A biological urine drug screening test determines recent use of a panel of substances, including cannabis/marijuana, opioids, cocaine, methamphetamine, and Mandrax (methaqualone). Victimization includes self-report of being beaten, attacked with a weapon, or forced to have sex during the previous 90 days. We assess if women living with HIV received treatment and took ART both biologically and by self-report. Self-report for ART refers to being prescribed ART, taking ART if prescribed, and missing any doses in the past 30 days. We also examine measures of adherence included in the U.S. National Institute on Drug Abuse’s harmonization initiative [30]. To help interpret these data, we also collect self-reports of barriers to ART use.

#### Staff training and quality assurance

In addition to the outreach training, field staff receive hands-on training with the Principal Investigator and with a guided field manual. They also receive ongoing training and support for the various expressions of emotional distress and crisis management. Interventions and interviews are audiotaped for quality assurance and all files are checked by a staff member and then checked again and signed off by the Field Project Manager. Training for staff also covers confidentiality and ethics. All staff members must sign a confidentiality agreement. They are also educated on their responsibilities for securing the consent forms and screeners and on the confidentiality requirements of the project.

#### Data collection, data management, and quality assurance

To protect confidentiality, the study assigns each participant a unique study identification code (ID). This ID is the only link between the behavioral and biological data and the identifying information collected for locating participants for their follow-up interviews. Locator information is stored separately from other data in a double-locked file cabinet that is in a locked room with restricted access.

Data collection for this study is conducted by highly trained local staff that develop a rapport with the study participants to engender trust and elicit the most accurate data possible. Highly trained local interviewers administer questionnaires using CAPI software that has been programmed to check that responses to each question are within the valid range, that responses to different questions are logically consistent, and to skip questions that are not applicable. Biological testing information is keyed into the same software system and rechecked for accuracy. Data are transmitted each day from the field site to secure servers at RTI’s headquarters in the United States. The US-based Data Manager reviews additional automated quality control checks that the software generates each day. The Principal Investigator, other members of the research team, and the field staff also receive these reports. If any critical inconsistencies are noted, the Data Manager contacts the Field Project Manager who works with the field staff member who collected or entered the data to resolve the inconsistency.

#### Sample size and power

The sample size was lowered to 600 from 1050 as originally planned. The original sample size was calculated on the basis of an anticipated HIV prevalence of 30%; however, HIV prevalence in the sample is 55%. Accordingly, the smaller sample (n = 600) will allow for the identification of a clinically meaningful effect with sufficient statistical power, while accounting for logistical difficulties, including a citywide study, limited structural resources, increased costs, and other factors outside the control of the study. We assume 14 clusters, approximately 30 observations per cluster and 20% attrition, yielding a final sample size of about 480 respondents at 12-month follow-up. This allows us a medium to strong likelihood of detecting an effect of the intervention assuming a strong effect (based on Cohen’s beta of 0.6). This would translate to an approximately 10% to 15% difference in the outcomes for any behavioral outcome (e.g., reductions in AOD use, number of instances of unprotected sex). We would not be able to detect mild to weak effects in analyses that consider the mediation of the effect of the intervention through some cognitive outcome, such as intentions/self-efficacy/knowledge/gender power. The reduction in power also greatly reduces the likelihood of testing whether the intervention yielded modification effects across the levels of some covariate and mediational effects as well. However, we will examine the distribution of the variables and reestimate power given the final sample size and variance estimates. No outcome or mediator/moderator analyses will be conducted unless there is strong power (e.g., Beta greater than .8, for a 2-tailed test and p = .05).

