#### Analysis

We will first conduct descriptive statistical analysis of baseline variables and clinical characteristics of the two intervention arms to examine the extent, if any, of baseline or clinical imbalances between the two arms using contingency table analyses (Mantel-Haenszel for categorical and analysis of variance for continuous variables). The analysis will center around estimating the impact of the intervention on each of the primary study outcomes, observed at baseline and 6- and 12-month follow-up visits, using all available cases consistent with an intent-to-treat method. In addition to evaluating changes in each outcome by intervention arm at 6-month follow-up, the analysis will examine whether the changes are sustained or decay at 12-month follow-up. Given the longitudinal nature of the data, our primary analytic strategy will apply a generalized estimating equation (GEE) modeling approach to account for the multiple dependencies of repeated measures collected on the same individuals over time, and the clustering of the outcomes by community. Because the communities may range from 5 to 100 cases, the generalized linear/nonlinear mixed model (e.g., hierarchical linear modeling or multilevel modeling with random effects) would likely face problems with convergence given the heterogeneity in the variation between communities. Therefore, we opt for a statistical strategy that treats this level of clustering as a nuisance parameter, and thereby estimating the population-averaged effects of the outcomes for subjects sharing the same profile of individual and community-level characteristics. For outcomes with binomial or count distributions, the logit link will be specified to obtain effect estimates of the magnitude of differences between arms within each follow-up visit. For continuously distributed outcomes, an identity link function will be specified. We expect that we will estimate the working correlation matrix at the temporal level using a first-order autoregressive structure (AR-1) and an exchangeable correlation matrix at the community-level, thereby allowing the subjects within each cluster to be constrained to equality but freeing the estimates between clusters.

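### The sample-size paragraph's cluster size does not fit its own 600 and 480, and its 10-15% difference, read as absolute points on condom use, mostly falls short of its own 0.8 power bar

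*Protocol article*

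**What the plan says.** All the power statements are in the protocol article, under Sample size and power. Enrolment was cut from 1050; Table 1 records the change as "Reduced proposed sample from 1050 to 600 minimum". The inputs and the resulting total are given in one sentence: "We assume 14 clusters, approximately 30 observations per cluster and 20% attrition, yielding a final sample size of about 480 respondents at 12-month follow-up".

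The power claim is verbal: "This allows us a medium to strong likelihood of detecting an effect of the intervention assuming a strong effect". The strong effect is a value of 0.6 credited to Cohen and called beta, with no scale defined. The next sentence converts it: "This would translate to an approximately 10% to 15% difference in the outcomes for any behavioral outcome". The examples given there are AOD use and a count of unprotected sex acts. The same paragraph says that "the smaller sample (n = 600) will allow for the identification of a clinically meaningful effect with sufficient statistical power". It ends by making every outcome analysis conditional on power above 0.8, two-sided at 0.05; there, beta means power.

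Under Outcome measures, the primary outcome is binary: condom use at the most recent vaginal or anal intercourse. Under Analysis, zone sizes are expected to vary: "Because the communities may range from 5 to 100 cases".

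**The concern.** The sentence presents 480 as the yield of inputs that cannot produce it. The next step equates a strong effect with a 10-15% difference, although on the usual Cohen scales a value of 0.6 is far larger than that for a proportion.

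The 10-15% figure is the only detectable difference in the article, so readers will judge a null result against it. It also bears on the article's own rule. If 10-15 points is the target and power is below 0.8, that rule could bar the primary analysis. If a standardised 0.6 is the target, the rule is met, but the percentage beside it misdescribes what the trial can detect.

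**Working it through.** **1. The plan's own total.** From Sample size and power: 600 enrolled, 14 clusters, about 30 per cluster, 20% attrition.

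- 600 x 0.80 = 480. The stated total reproduces.
- 14 x 30 = 420 if 30 is after attrition, which is 12.5% below 480.
- 14 x 30 x 0.80 = 336 if 30 is before attrition, which is 30% below 480.
- 420 / 0.80 = 525 enrolled would be implied by 30 completers per zone, not 600.
- Per zone, the stated totals need 600/14 = 42.9 enrolled and 480/14 = 34.3 followed.

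The input that does not fit is the cluster size.

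**2. What 0.6 means in percentage points.** The article gives no control rate, so 20-60% is assumed (20-70% for the log-odds reading).

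| Reading of 0.6 | Formula | Difference |
|---|---|---|
| Cohen's h | p2 = sin²(asin√p1 + 0.3) | 25.9-29.4 points |
| Cohen's d, logistic rule | OR = exp(0.6π/√3) = 2.97 | 21.7-26.4 points |
| Log-odds coefficient | OR = exp(0.6) = 1.82 | 11.0-14.8 points |

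Conversely, 10 points is h = 0.20-0.23 and 15 points is h = 0.30-0.34. The d reading falls to 10-15 points only at extreme control rates: 14.8 points from 10%, and 12.2 from 80%.

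**3. Power for 10 and 15 absolute points.** The setting is 480 followed (240 per arm), seven zones per arm, m = 34.3, two-sided 5%, t on 14 - 2 = 12 df (critical value 2.179), and equal zones. ICC and control rate are assumptions.

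- DE = 1 + (m - 1) x ICC
- n_eff = 240 / DE per arm
- λ = (p2 - p1) / √{[p1(1 - p1) + p2(1 - p2)] / n_eff}
- Power = P(noncentral t with 12 df and parameter λ exceeds 2.179)

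Example, 50% v 60%, ICC 0: λ = 0.10 / √(0.49/240) = 2.21, power 53%.

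Example, 50% v 65%, ICC 0.02: DE = 1 + 33.3 x 0.02 = 1.67, n_eff = 144, λ = 0.15 / √(0.4775/144) = 2.61, power 67%.

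| ICC | DE | 20 v 30% | 20 v 35% | 50 v 60% | 50 v 65% |
|---|---|---|---|---|---|
| 0 | 1.00 | 65% | 93% | 53% | 87% |
| 0.01 | 1.33 | 53% | 84% | 42% | 76% |
| 0.02 | 1.67 | 44% | 76% | 35% | 67% |
| 0.05 | 2.66 | 30% | 56% | 24% | 47% |

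Unequal zones lower these figures. With DE = 1 + [(1 + CV²)m - 1] x ICC and an assumed CV of 0.63, 50 v 65% at ICC 0.02 falls from 67% to 60%.

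A normal reference instead of t(12) is kinder. From 50%, 10 points has 60% at ICC 0; 15 points has 92%, 82%, 73% and 53% at ICC 0, 0.01, 0.02 and 0.05. From 20%, 10 points at ICC 0 has 72%.

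**4. Does the log-odds reading meet the bar?** For OR 1.82, control rates 20-70%, equal zones and t(12), power is 61-75% at ICC 0.01, 52-65% at 0.02 and 35-46% at 0.05.

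**5. Effect of 480 against 420.** For 50 v 65% at ICC 0.02 and t(12), power is 67% with 480 and 63% with 420.

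**6. Difference detectable at 80% power.** Solving step 3 for p2 with 480 followed:

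| Control rate | Zones | ICC 0.01 | ICC 0.02 | ICC 0.05 |
|---|---|---|---|---|
| 20% | equal | 14.1 | 15.9 | 20.4 |
| 50% | equal | 15.7 | 17.4 | 21.7 |
| 20% | CV 0.63 | 14.9 | 17.2 | 22.9 |
| 50% | CV 0.63 | 16.4 | 18.7 | 24.0 |

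**The case against.** **A reader might infer that 480 is an arithmetic error.** It is not: it equals the stated enrolment less the stated attrition. Changing the total to 420 or 336 would contradict the 600 given in three places. Only the cluster size is off.

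**A reader might infer that 0.6 cannot be a 10-15% difference.** That goes too far. The Analysis section plans a logit-link GEE, and a log-odds coefficient of 0.6 does give 11-15 points at control rates of 20-70%. The attribution to Cohen points to a standardised scale, so the defect is an undefined scale, not a proven wrong conversion. The log-odds reading still misses 0.8 at every ICC of 0.01 or more examined here.

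**A reader might infer that the trial cannot detect what it claims.** That does not follow from 420 against 480, which moves power by only a few points. The article promises no numerical power, and a standardised 0.6 is well covered: with 480 followed, equal zones and t(12), power is 96% at ICC 0.05 and 83% at 0.10. Yet the same paragraph also claims sufficient power and sets 0.8 as its bar.

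**Limits of the calculation.** The article does not say whether 10-15% is absolute or relative, and its examples are not the primary outcome. ICC, control rate and zone-size variation are assumed here; their absence from an article is not itself a fault. A 50% control rate is less favourable than 20%, so both are shown. The check uses one 12-month contrast, whereas the GEE also uses baseline and 6-month data. These points make the exact percentages conditional.

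**Zone sizes.** About 30 per zone can be an average, so it does not contradict a range of 5 to 100. The range matters only because it lowers power.

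**Mitigation.** The article says power will be re-estimated with the final sample and variances. That does not correct the published figures.

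**Conclusion.** The paragraph is wrong as written, in two limited respects.

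First, about 30 per cluster is inconsistent with 600 enrolled and 480 followed. Taken alone, this is minor.

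Second, the equation of a strong effect of 0.6 with 10-15% does not support the claim of sufficient power across that range. On Cohen's d or h the two figures do not match at mid-range control rates. On the log-odds scale they match, but power then falls short of 0.8 once there is modest clustering.

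If 10-15% means absolute points on the primary outcome, 10 points misses the bar from either assumed control rate even with no clustering, and 15 points meets it only at very low ICC. The shortfall at 10 points does not depend on the choice between t(12) and a normal reference. For 15 points it depends on the assumed ICC and control rate, with the crossing at an ICC of about 0.01-0.02 from 20% and below 0.01 from 50% under t(12).

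**What to change.** Keep 600 enrolled and 480 followed, and correct the cluster size to about 43 enrolled and 34 followed per zone on average.

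Name the scale of 0.6 and say whether 10-15% is absolute or relative, or drop the statement that one translates to the other. Use a term other than beta for either the effect or the power, since the paragraph uses it for both.

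Restate the detectable difference for condom use at last sex at 80% power, with the control rate, ICC range and zone-size variation stated. On the assumptions above it is roughly 14-24 points for ICC 0.01-0.05 and control rates of 20% or 50%.

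This costs a recalculation and a less favourable stated figure. Enrolment, design and primary analysis do not change.
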